### Baseline characteristics

To characterise the sample, demographic information will be assessed by self-report including age, gender (including gender minorities such as being trans or non-binary), sexuality, ethnicity and marital status. Self-harm rates are elevated amongst the LGBTQ + community and hence it is important to monitor sexual orientation and gender minority status [57–59]. Health information including current and past physical and mental health diagnoses, and current and past receipt of therapy and medication will also be assessed by self-report. To further assess psychopathology, the MINI [49] will be administered at baseline and researchers will receive training in using the MINI. To minimise participant burden, only the MINI subscales relating to depression, anxiety disorders, mania, and psychosis, will be administered. Since self-harm is associated with socioeconomic deprivation [60], this will be recorded at baseline using the Indices of Multiple Deprivation (IMD; [61]). The IMD is a widely used measure that provides an indicator of socioeconomic deprivation based on participants’ postcode.

### Outcomes

#### Primary outcomes

The primary outcomes will relate to feasibility and acceptability. Table 1 presents the primary outcomes and associated progression criteria for the trial. A traffic light system (green = progress to definitive trial; amber = modification needed; red = do not progress) has been adopted to guide the decision to progress to a larger trial. A final decision concerning progression to a definitive trial will be made by the RELATE research team based on these outcomes, with support from the TSC. Acceptability will be further determined through the qualitative component of the trial. The safety of the intervention and trial procedures will be evaluated through the monitoring of AEs. This information will be supplemented with evidence of adverse experiences identified during qualitative interviews with participants. Participants receiving CAT will also be asked to complete the Adverse Effects in Psychotherapy measure [62], a self-report questionnaire that measures perceived adverse experiences that can occur in psychotherapy.

**Table 1 Tab1:** Feasibility progression criteria with traffic light indicators

Outcome	Criterion	Green	Amber	Red
Recruitment	Ability to randomise 60 participants in a 12-month recruitment window	> 80%	60–79%	< 60%
Retention	Percentage of participants completing the 12-week assessment as potential primary outcome timepoint	> 80%	60–79%	< 60%
Outcome suitability	Missing data on candidate primary outcomes (SITBI; ABUSI) at 12-week assessment	< 15%	16–25%	> 25%
Adherence	Percentage of participants receiving the minimum dose of therapy (≥ 4 sessions) within 10-week treatment window	> 80%	60–79%	< 60%

*ABUSI* Alexian brothers urges to self-injure scale, *SITBI* Self-injurious thoughts and behaviours interview-short form

#### Secondary outcomes

Data pertaining to pilot clinical outcomes and putative therapy mechanisms will also be collected. Measure completeness (amount of missing data), statistical properties (e.g. variance, floor and ceiling effects), and qualitative feedback from participants will help inform the choice of primary outcomes for a future definitive trial. The anticipated primary outcome for a definitive trial is self-harm repetition, recorded via the SITBI [48], and self-harm urges, recorded via the Alexian Brothers Urges to Self-Injure scale (ABUSI; [63]), at post-treatment (12 weeks post-randomisation). Table 2 lists the outcome measures and the schedule for when they will be administered.

**Table 2 Tab2:** Overview of assessment schedule

Assessment	Baseline	12 weeks	18 weeks
Demographics	x	-	-
MINI	x	-	-
SITBI	x	x	x
ABUSI	x	x	x
ESIQ	x	x	x
PSQ	x	x	x
KDS	x	x	x
IIP-32	x	x	x
EQ-5D-5L	x	x	x

*ABUSI* Alexian brothers urges to self-injure scale, *ESIQ* Experiences of self-injury questionnaire, *IIP-32* Inventory of interpersonal problems–32, *KDS* Kessler distress scale, *MINI* Mini international neuropsychiatric interview, *PSQ* Personality structure questionnaire, *SITBI* Self-injurious thoughts and behaviours interview-short form

#### Self-harm behaviour and urges

The SITBI [48] is a widely used structured interview that assesses self-harm-related thoughts and behaviour, capturing information on the occurrence, frequency and characteristics of these thoughts and behaviours over a person’s lifetime. In this trial, the modules relating to suicidal ideation, suicide attempts, and non-suicidal self-injury will be administered. Responses will be used to determine the presence and frequency of self-harm (encompassing suicide attempts and non-suicidal self-harm) over the follow-up period. We will calculate rates of suicidal behaviour and non-suicidal self-injury separately, given the argument that there can be important distinctions between these behaviours [18]. The SITBI has good inter-rater reliability and concurrent validity [48]. Urges to self-injure will be assessed using the ABUSI [63]. This is a five-item questionnaire assessing the severity of urges to self-injure over the preceding week. Scores range from 0 to 30 with higher scores indicating more severe urges to self-injure. The ABUSI shows good validity and reliability, and the single-factor structure has been supported [s63].

#### Self-harm dependence

Dependence on self-harm will be assessed with the positive beliefs subscale of the Experiences of Self-Injury Questionnaire (ESIQ; [64]). This eight-item questionnaire has scores ranging from 0 to 32, with higher scores indicating a greater perceived dependence on self-harm (i.e. greater perceived reliance and need). The factor structure, concurrent validity and reliability of this measure have been supported [64].

#### Self-concept stability

The Personality Structure Questionnaire (PSQ; [65]) will be used to assess the stability of self-concept. The questionnaire features eight items with scores ranging from 8 to 40, and higher scores indicating instability in one’s sense of self (i.e. perceived marked shifts in mood and personality). The scale is often used as a mechanistic measure for CAT [66, 67] since one hypothesised mechanism of change in CAT is the development of a more coherent and stable self-concept [26]. The reliability and validity of this measure have been supported [65, 68, 69]. Results regarding the factor structure of the questionnaire vary, but a single-factor or component solution has been most widely supported and adopted, and so will be used here [63, 66, 67].

#### Emotional distress

Self-harm is often linked to emotional distress [12]. The Kessler distress scale (K10; [70, 71]) is a widely used questionnaire of emotional distress over the past 30 days. The questionnaire has ten items, with scores ranging from 10 to 50. Higher scores indicate greater emotional distress. The scale has good reliability, concurrent validity and distinguishes well between individuals with and without mental health disorders [71, 72].

#### Interpersonal problems

Interpersonal difficulties can often be interconnected with self-harm [39]. The Inventory of Interpersonal Problems-32 (IIP-32; [73]) will be used to assess interpersonal difficulties. The questionnaire has 32 items, with scores ranging from 0 to 128. The use of a single total score as a measure of interpersonal difficulties is commonly adopted, with higher scores indicating greater difficulties. The scale has good internal reliability and was found to distinguish between the general population and psychology outpatient samples [74]. Both subscale scores and a total score have been used [74], with the latter being adopted for this trial.

#### Quality of life

The EQ-5D-5L [75] is a self-report measure of general health status. Respondents are asked to describe their health on that day in terms of mobility, self-care, engagement in activities, pain/discomfort, and depression/anxiety. A global rating of health on a scale from 0 to 100 is also requested. An index value representation of overall health can be obtained by applying a formula to respondents’ scores. A systematic review encompassing 99 papers using this tool concluded the scale had excellent psychometric properties [76].

#### Health and social care resource use

A bespoke self-report measure of health and social service use, based on the Client Service Receipt Inventory [77], designed with the involvement of experts by experience, will be completed at 18 weeks to capture this information across the course of the trial.

### Data collection

Assessment sessions will be at a place of mutual convenience for the researcher and participant. This could be the participants’ own home, a university room, a GP surgery, a mental health service, or another NHS building. We will also allow for assessment and interventions to be carried out online via video call or over the telephone in accordance with the lead Trust’s policies around remote consultation. Remote appointments allow for greater flexibility and so will help improve retention. Researchers will remain in contact with participants between assessment points, and send reminders of appointments by phone, email, and text. Participant newsletters will also be sent to help keep participants engaged in the trial. Participants will have the option to withdraw from the trial at any time or may withdraw from therapy but otherwise remain involved in the trial and still complete follow-up assessments.

During assessments, a researcher will be present to administer assessments and help participants complete questionnaires. Participants may take breaks as needed. Data will be collected on a paper Case Report Form (CRF). A copy of the CRF can be requested from the research team (excluding copyrighted material). Researchers will receive training in conducting assessments and issues in conducting assessments will be a standing item during weekly supervision meetings.

### In-therapy measures of idiographic change

As part of CAT, participants are asked to complete a personalised monitoring form within sessions that focus on the Target Problems (TPs) and Target Problem Procedures (TPPs) that are focal to self-harm, with the support of their therapist. TPs refer to a type of self-harm, whilst TPPs refer to the patterns of thinking, feeling and behaviour (called “procedures”) associated with the self-harm [26]. In the present trial a TP might be specifically self-harm, but might also be an associated underlying issue. For example, a TP might have feelings of shame, and a TPP might be a pattern of social withdrawal and self-criticism that contributes to feelings of shame that then drive self-harm. TPs and TPPs will be identified and rated in terms of recognition and revision at each session for the preceding week, using standard TP and TPP monitoring forms. These data provide an additional idiographic outcome that can be tracked across therapy sessions for those in the CAT arm.

### Qualitative process evaluation

Qualitative semi-structured interviews will be undertaken with a subset of participants from both arms of the trial. Whilst the small numbers prevent any formal stratification of the sample by factors like gender or ethnicity, purposive sampling will be adopted, with the aim of increasing the diversity with regards to trial engagement (i.e. people who withdrew from therapy or the trial), gender, ethnicity, sexual minority status and socioeconomic deprivation of those individuals invited from the larger sample to participate in the interviews. As participants become eligible for the interviews their demographic characteristics will be reviewed against the pool of participants that have already been interviewed. Where participants differ from the existing pool, reflecting some under-represented characteristics, they will be preferentially selected for the interviews. This process will be followed for participants in both trial arms.

Interviews will be guided by an interview schedule and be undertaken either in person or remotely via video call or telephone. Interviews will be audio recorded using an encrypted device. For those in the CAT arm interviews will focus on the acceptability of the therapy, perceived benefits and mechanisms of action, challenges to engagement, adverse experiences, and contextual factors seen to affect the impact of intervention. For participants in the TAU arm of the trial, interviews will concern the acceptability of trial procedures, including randomisation, assessments, and ongoing contact with the research team. The theoretical framework of acceptability will be used to help guide interviews and interpretation [78].

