A major challenge for expensive RCTs is recruitment and retention [46]. RELATE will indicate whether it will be feasible to undertake a large-scale trial of CAT for self-harm. In addition, RELATE will generate data on acceptability, safety, patient experience, the performance of different clinical outcomes, preliminary evidence of the promise of patient benefit and the amount of resources consumed. The central aim of the current trial is to evaluate the feasibility of an 8-session CAT for adults experiencing self-harm. The goal for a definitive trial would be to see how CAT compared to current treatment and so CAT will be compared with treatment-as-usual (TAU). Feasibility will be assessed against pre-specified progression criteria in terms of recruitment and retention of participants, and missing data on outcome measures. The trial will also determine what resource data can be collected reliably to conduct an economic evaluation. Acceptability of both the therapy and trial procedures will also be assessed via therapy adherence rates and qualitative interview data. Safety of the therapy and trial procedures will be evaluated via monitoring of Adverse Events (AEs), and participant-reported adverse experiences recorded via questionnaire and qualitative interviews. The RELATE trial has not been designed to determine treatment efficacy. Nonetheless, treatment effects on secondary clinical outcomes (e.g. self-harm behaviour and urges) will be estimated to help inform parameters required for a larger-scale trial evaluation (e.g. variance in outcome measures). In keeping with the approach of CAT, within the treatment arm of the trial, we will also monitor individual patient change on idiographic session-by-session outcomes as a further initial evaluation of the potential clinical promise of the therapy. TAU may be variable, with factors such as issues with treatment access amongst those who self-harm contributing to this [23], so this will be monitored.

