### Sample size

We will aim to recruit 60 people for the study (30 per trial arm). This number will be sufficient to estimate key parameters to inform a future definitive trial, (e.g. the standard deviation of key outcomes; the attrition rate), to an adequate degree of precision [79]. For the qualitative process evaluation, a target of 15 participants from the CAT arm of the trial, and 5 participants from the TAU arm will be sought. Drawing on the principles of information power [80] we note the sample specificity is dense and the qualitative process evaluation has a relatively narrow aim, but there is no guiding theory and a cross-case analysis is sought. A sample size of 20 overall therefore appears adequate. The imbalance between CAT and TAU arms reflects our particular interest in the experience of the therapy itself, and the anticipation that experiences of the therapy may be more complex and varied, than experiences of being in the TAU arm, requiring a larger sub-sample. The idiographic change analysis of TP and TPs will be based on the 30 participants in the CAT arm.

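### Acceptability of trial procedures is listed as an interview topic for the TAU arm only (target 5), so direct evidence on how randomisation was experienced would come mainly from people not allocated to CAT

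*Protocol article*

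**What the plan says.** The Introduction sets the aim without limiting it to one arm: "Acceptability of both the therapy and trial procedures will also be assessed via therapy adherence rates and qualitative interview data". The Primary outcomes section adds that the qualitative component will further inform the judgement on acceptability.

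The Qualitative process evaluation section then gives each arm its own topics. For CAT: "For those in the CAT arm interviews will focus on the acceptability of the therapy, perceived benefits and mechanisms of action, challenges to engagement", followed by adverse experiences and contextual factors. For TAU: "For participants in the TAU arm of the trial, interviews will concern the acceptability of trial procedures, including randomisation". The TAU list also takes in the assessments and continued dealings with the researchers. Randomisation, assessments and research contact do not appear in the CAT list, and adverse experiences do not appear in the TAU list.

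The Sample size section sets the numbers: "a target of 15 participants from the CAT arm of the trial, and 5 participants from the TAU arm will be sought". It concludes "A sample size of 20 overall therefore appears adequate" and explains the split: "The imbalance between CAT and TAU arms reflects our particular interest in the experience of the therapy itself", adding that therapy experiences are expected to be the more complex and varied. The evidence needed on trial procedures is not part of that explanation.

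**The concern.** A feasibility trial should tell the team whether people accept being randomised, assessed and followed up. Everyone randomised can speak to that, and how someone feels about randomisation may well depend on the arm they were given. Assigning the topic to the TAU arm makes the evidence both small and one-sided: few informants, all of whom were allocated to the arm without CAT.

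Some trial experiences also belong to the CAT arm alone, such as completing trial assessments after a course of weekly sessions, or having sessions recorded for competence rating. The sampling plan deliberately seeks people who withdrew from therapy or from the trial, in both arms. Yet the topics listed for a CAT participant who left the trial do not include the trial's own procedures. What is at stake is the quality of the advice passed to the definitive trial's design, not any numerical result of this one.

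**Working it through.** **1. Reproduce the plan's figure.** 15 CAT + 5 TAU = 20 interviews, as the Sample size section states. The number is justified by information power, so there is no formula to re-run.

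**2. Share of interviews for which trial procedures are a listed topic.**
- Of all interviews: 5/20 = 25%.
- Of the TAU arm: 5/30 = 17%.
- Of all randomised: 5/60 = 8%.
- Of the CAT arm: 0/30, as the topic lists are written.

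**3. Which sources can inform acceptability of trial procedures?** The Introduction names two.
- Therapy adherence is defined in Table 1 as receiving at least 4 sessions. It concerns the therapy and can only be observed in the CAT arm, so it says nothing direct about randomisation.
- That leaves the interviews, and the topic lists point this question to TAU.

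**4. What other sections cover.**
- Primary outcomes and Introduction: adverse experiences are drawn from interviews with participants, with no arm limit.
- Secondary outcomes: qualitative feedback from participants informs the choice of measures, again with no arm limit. This bears on assessments.
- Table 1: recruitment, retention and missing data are measured across the trial. They can show that people declined or left, but not how randomisation was experienced.

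None of these asks CAT participants about randomisation or research contact, so the gap is clearest there.

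**5. Illustration only.** Suppose a view is held by a proportion p of participants, interviewees are a random sample, and everyone asked voices the view. The chance of hearing it at least once is 1 − (1 − p)^n. Neither p nor random sampling comes from the protocol, which samples purposively.

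| Assumed p | n = 5 | n = 20 |
|---|---|---|
| 0.05 | 23% | 64% |
| 0.10 | 41% | 88% |
| 0.20 | 67% | 99% |
| 0.30 | 83% | 99.9% |

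The n = 20 column also assumes the same p in both arms. Two extremes show how much that matters:
- View held only in the TAU arm: adding 15 CAT interviews changes nothing. At p = 0.10 in that arm the chance stays at 41%.
- View held only in the CAT arm: 5 TAU interviews can never reveal it. With 15 CAT interviews the chance is 1 − 0.9^15 = 79% at p = 0.10 and 1 − 0.8^15 = 96% at p = 0.20.

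The gain therefore lies chiefly in views specific to, or shared by, the CAT arm. The table should not be read as the operating characteristics of this design.

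**The case against.** The strongest reply is that the protocol never says CAT participants will not be asked. Saying that an interview will focus on something states emphasis. The interviews are semi-structured, the interview schedule is not shown, and an article normally condenses a topic guide to a sentence or two per arm. The Introduction's aim carries no arm limit. This stands in part: a reader might infer that views on trial procedures will come from 5 people and nobody else, and the text does not support that. It supports *mainly*, not *only*. What survives is that the article states who is asked what, and the stated TAU list contains randomisation while the stated CAT list does not. That is an allocation of topics, not merely an omitted detail.

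Second, other evidence exists in both arms, as set out in the working: adverse experiences, feedback on measures, and the quantitative progression criteria. This also stands, and it narrows the point to randomisation and research contact more than assessments.

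Third, detection probabilities do not belong to a purposive sample sized by information power and analysed by reflexive thematic analysis. This is right. They also sit awkwardly with the argument that the arms may differ, since a straight comparison of 5 with 20 assumes they do not. The point does not depend on them.

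Finally, the 15:5 split has a reasoned basis. Agreed; nothing here requires changing it. It might also be tempting to say that TAU interviewees had no therapy. The Treatment as usual section allows other talking therapies, so the accurate statement is that they were not allocated to CAT.

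**Conclusion.** The point holds in a limited form. As described, direct qualitative evidence on how randomisation and research contact were experienced would come mainly from a target of 5 people allocated to TAU, against an aim that covers trial procedures generally and a trial in which all 60 participants undergo them. For assessments and adverse experiences the gap is partial.

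The conclusion assumes that the topic lists are followed roughly as printed. If the interview schedule already asks CAT participants about trial procedures, only the description needs correcting. No stated figure is wrong, and the progression criteria are unaffected. The point is minor: a low-cost improvement to the plan.

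**What to change.** In the Qualitative process evaluation section, state that all 20 interviews include the same short block on trial procedures (randomisation, assessments, contact with the research team) and on adverse experiences of taking part. The therapy block is then added for CAT participants. Keep the 15:5 split and its rationale. In the analysis, report views on randomisation with the interviewee's arm shown.

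The cost is a few extra minutes (an assumption, as the protocol gives no interview length) in 15 interviews already planned, with slightly longer transcripts to code. The number of interviews does not change. There is some risk of diluting the time spent on therapy, which a brief block limits. If the schedule already contains such a block, one clarifying sentence is enough. If detection probabilities are used to support the change, label them as illustrative, with assumed prevalence and random sampling.
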